The efficacy and risks of expanded newborn screening for IEM require careful evaluation before it can be accepted as a mandatory national program. The lack of epidemiological data on the incidence of IEM is one of the reasons for the delay in the development of proper population-based newborn screening for IEM using the LC-MS/MS method in Kazakhstan. Currently, NBS is being conducted in Kazakhstan for two hereditary diseases - phenylketonuria (PKU) and congenital hypothyroidism, the most represented screening diseases in most countries (Therrell and Padilla, 2018). This nationwide NBS program based on biochemical tests started in 2007 (Loeber et al., 2021), long after NBS was introduced in the United States in 1963 (Guthrie and Susi, 1963). Besides, in Kazakhstan, before the present study, state-funded MS/MS selective screening programs were implemented as sporadic pilot projects in some regions of the country without completion. Reports on these projects have not been published in peer-reviewed journals. As MS/MS neonatal screening is not mandatory in Kazakhstan, there are no uniform technical specifications for IEM screened by MS/MS in pilot studies. Hence, data on the frequency of IEM at the national level are not presented. For a country with no mandatory ENBS MS/MS program, selective screening can become essential for diagnosing IEM. The present research aims to develop and validate the LC-MS/MS method for simultaneously determining 51 metabolites in dry blood spots for IEM screening, as well as clarifying age-related ranges for AAs, ACs, and SuAc in Kazakhstan children. It is commonly accepted that children need to use reference populations that reflect changes associated with growth and development (Dogan et al., 2017). Therefore, one of the objectives of this study is to set reference intervals for the concentration of amino acids, succinylacetone, and acylcarnitines in dry blood spots for different age groups in the range from 1 day to 18 years. Owing to historically established social-cultural traditions supported by the legislation, consanguineous marriages are practically absent in Kazakhstan. This distinguishes Kazakhstan from many Asian and European countries, where consanguineous marriages are a real problem and, according to researchers, they are one of the reasons for the relatively high incidence of certain groups of IEM identified during selective newborn screening (Nagaraja et al., 2010; Al Riyami et al., 2012; Golbahar et al., 2013; Selim et al., 2014; Hassan et al., 2016; Demirelce et al., 2020; Gayduk et al., 2022; Magdy et al., 2022).

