**FIGURE 2 F2:**
[figure not shown]
Sites for data collection throughout western Kazakhstan.

Children from the western Kazakhstan population with suspected metabolic disorders are examined for congenital metabolic disorders and referred by primary care neonatologists and pediatric consultants between October 2022 and August 2024 based on their clinical symptoms associated with metabolic disorders. The study includes newborns and children being treated in maternity wards and pediatric clinics of 7 pediatric hospitals in the region. Patients with suspected IEM from all sites are referred to the Regional Tertiary Care Center or the Mother and Infant Health Center in Aktobe, or their samples are sent from other involved hospitals. Patient information is obtained from the Individual Registration Cards (IRCs) completed by study participants. The completed questionnaires are checked by the researchers. In case of improper collection, data must be removed from the study if it is impossible to check adequately. The IRC sample and other supplementary materials are placed in the *clinical. trials.gov* Register (https://www.clinicaltrials.gov/study/NCT05910151) and a publicly available repository (https://osf.io/cmrh7/).

To set reference values of 15 AAs, 35 ACs, and SuAc, healthy participants without any disease are included in the study. A total of 750 healthy male and female children aged 1 day to 18 years are recruited based on random selection. Participants will be balanced by gender and place of residence. Considering the distribution of urban and rural populations in western Kazakhstan, approximately half of them will be selected in urban areas, the other half in rural areas. A summary of the age, gender, and geographic distribution of study participants will be presented in Table 1.

**TABLE 1 T1:** Demographic data to be collected on study participants.

Variables	Selective screening (n = 1,500)	Healthy children (n = 750)
Age in days, years (median, range)		
Weight in grams, kilograms (median, range)		
Gender		
Male, n		
Female, n		
Geographic distribution		
Aktobe province		
Atyrau province		
West Kazakhstan province		
Mangystau province		
Urban population		
Rural population		

Screened children with positive first-level LC-MS/MS test results will be referred for second-level screening.

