### 3.2 Statistical analysis

Shapiro-Wilk and Kolmogorov-Smirnov tests will be used to check the normality of the distribution. As a rule, the distribution of free carnitine and acylcarnitines concentrations in whole blood differs from normal (Manta-Vogli et al., 2020). If the data sets show a normal distribution, M (mean) and standard deviation (error of the mean) will be used for descriptive statistics of the samples. Parametric tests will be used to test for differences between AA and AC concentrations depending on various factors (gender, place of residence) (t-test, analysis of variance (ANOVA) with or without Tukey’s test). If the data sets do not show a normal distribution, Me (median) and quartiles (interquartile range IQR) will be used for the descriptive statistics of the samples. Non-parametric tests (Mann-Whitney U-test, Kruskal-Wallis H-test without or with subsequent *post hoc* comparisons using U-test will be applied to test the differences mentioned above. The Pearson χ^2^ criterion will be applied to identify intergroup differences for categorical variables. If the distribution of analytes is skewed, reference intervals in the healthy control group will be determined nonparametrically and correspond to the 0.5–99.5th percentile of the experimental distribution. Correlations between body weight, and concentration of each analyte will be performed using corresponding tests.

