Indices of sensitivity (Sn), specificity (Sp), positive predictive values (PPVs), and negative predictive values (PVN) will be calculated for each diagnostic test under consideration. PPVs will be calculated by dividing the total number of true positive cases by the total number of true positive and false positive cases. The detection rate will be calculated by dividing the number of cases diagnosed by the number of screened children with suspected metabolic disorders. Multiple linear regression coefficients will be calculated to assess the relationship of each analyte with the factors of gender, weight, and place of residence. Due to the number of variables subjected to analysis, and the anticipated presence of multiple outcomes, the included tests may not be sufficient. So, the cluster analysis and, possibly, the decision-tree method will be applied. Decision trees break down complex data into more manageable parts, beneficial in prediction analysis, data classification, and regression. A dimensionality reduction method, principal component analysis (PCA), will also be applied. Two-sided levels <0.05 are assumed to be statistically significant. Statistical analysis will be carried out using the statistical packages IBM SPSS v. 23.0 (IBM, Armonk, NY, United States), Statistica (StatSoft, Inc., Tulsa, OK, United States, v. 10), and R 3.3.2 (R Foundation for Statistical Computing, Vienna, Austria.)

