#### 3.2.1 Descriptive statistics and group comparison

Descriptive statistics and reference intervals for whole blood concentrations of 15 AAs, 35 ACs, and SuAc in healthy children divided into subgroups according to gender will be presented in tables. For each analyte in the healthy control group, the upper cut-off will be set above the 97.5^th^ percentile, while the lower cut-off will be set below the 2.5th percentile. Differences in the distribution of amino acids, acylcarnitines, and succinylacetone between groups, as determined using the Mann-Whitney and Kruskal-Wallis tests, will be noted in the table if found.

Cut-off values for analytes and their ratios for selective screening of AAD, OA, and FAOD presented in Table 3 will be pointed out. The results of determining the analytes in DBS in children of the healthy control group will be compared with those of previously published studies in other populations. According to the inclusion criteria, healthy newborns in the reference group must be full-term (born at 37–42 weeks). However, it should be taken into account that some of the newborns at risk for IEM are born prematurely. In this regard, it is also necessary to determine reference intervals for the concentrations of 15 AAs, 35 ACs and SuAc in dried blood spots of premature infants who do not have clinical symptoms of IEM.

Comparison of mean concentrations (Me, range) of analytes between groups of high-risk children and healthy controls will be presented.

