As such, this study is the first in Kazakhstan and Central Asia to assess the prevalence of IEM among children at risk. Also, reference values of metabolites for three different age groups of the child population in western Kazakhstan will be established for the first time. Our research can be considered a pilot and expected to give an impulse to launch a nationwide ENBS program using LC-MS/MS. Overall, the study will further develop the national as selective as expanded newborn screening programs.

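### Age-specific reference values are a stated objective and part of the first primary outcome, but no sampling or analysis step that sets or compares limits uses age

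*Protocol article*

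**What the plan says.** **What is promised.** Section 1 of the protocol article lists age among the factors on which cut-offs depend and says laboratories should establish age-related ranges before screening. It names as one objective to "set reference intervals for the concentration of amino acids, succinylacetone, and acylcarnitines in dry blood spots for different age groups", from 1 day to 18 years. The first primary outcome in Section 3.1 is metabolite values in newborns and in children of different age groups. Section 4 says that "reference values of metabolites for three different age groups of the child population in western Kazakhstan will be established for the first time".

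**What is planned.**
- Control sampling (2.2.2): "Participants will be balanced by gender and place of residence".
- Source of the limits (2.3.4): the 750 healthy children, with no age split stated.
- Group tests (3.2): differences in concentration "depending on various factors (gender, place of residence"). The correlations are with body weight.
- Regression (3.2): "Multiple linear regression coefficients will be calculated to assess the relationship of each analyte with the factors of gender, weight, and place of residence".
- Reference intervals (3.2.1): concentrations "in healthy children divided into subgroups according to gender will be presented in tables". The cut-offs are percentiles of the healthy control group.
- Comparison tables (3.2.2): gender and body weight, in the high-risk and healthy groups.

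Age appears elsewhere as a row of Table 1, as age at diagnosis and a matching factor for displayed individual profiles (3.3), and in the description of onset and symptoms (Task 3, Section 4). None of these sets a limit.

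**The concern.** The article argues that limits in children must follow age, makes that an objective and a primary outcome, and then names a different set of stratifiers and covariates. This is more than missing detail. The split of the reference tables (gender) and the regression terms (gender, weight, residence) are stated outright, and gender has its own subsection.

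Three things are at stake:
- **Screening results.** The Abstract says these will be interpreted against the study's own reference values. Results beyond the limits lead to retesting and confirmatory tests (2.3.1, 2.3.5). A limit that does not fit a child's age therefore carries through to the second primary outcome, the detection rate and the predictive values.
- **Interpretation of weight.** Healthy newborns enter at 2,500–4,000 g (2.2.3) and the oldest children are 18 years old. Weight and age must move together over that range, so a weight coefficient without age in the model cannot be read as an effect of weight.
- **Size of the age groups.** Age is not a balancing factor, so nothing in the text protects any one age group from being too small for its own percentiles. Analysis cannot repair that afterwards.

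**Working it through.** **1. Promise against plan.** The article gives no numerical claim on this point to reproduce. Side by side:

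| Step | Section | Factors named | Age? |
|---|---|---|---|
| Objective | 1 | age groups | yes |
| First primary outcome | 3.1 | newborns, age groups | yes |
| Stated product | 4 | three age groups | yes |
| Control balancing | 2.2.2 | gender, residence | no |
| Source of limits | 2.3.4 | 750 healthy children | no |
| Group tests | 3.2 | gender, residence | no |
| Correlation | 3.2 | body weight | no |
| Regression | 3.2 | gender, weight, residence | no |
| Reference tables and cut-offs | 3.2.1 | gender | no |
| Comparison tables | 3.2.2 | gender, body weight | no |

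**2. What a limit across all ages would do: two groups.** The documents give no age shift, so these inputs are assumptions: a lognormal analyte; newborns one third of controls; newborn median *r* times that of older children, with *r* from 1.3 to 2.0; log-SD *σ* from 0.25 to 0.35. With the older children's median set to 1, the upper limit on the log scale, *U*, solves

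(1/3)·Φ((U − ln r)/σ) + (2/3)·Φ(U/σ) = 0.975.

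The shares above the limit are 1 − Φ((U − ln r)/σ) in newborns and 1 − Φ(U/σ) in older children. The limit divided by the older children's own 97.5th percentile is exp(U − 1.96σ).

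| r | σ | U | Newborns above | Older above | Limit ÷ older children's own |
|---|---|---|---|---|---|
| 1.3 | 0.25 | 0.642 | 6.5% | 0.5% | 1.16 |
| 1.3 | 0.35 | 0.819 | 5.6% | 1.0% | 1.14 |
| 1.5 | 0.30 | 0.848 | 7.0% | 0.2% | 1.30 |
| 2.0 | 0.25 | 1.053 | 7.5% | 0.0% | 1.76 |
| 2.0 | 0.35 | 1.199 | 7.4% | 0.0% | 1.67 |

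The target is 2.5% in each group. Check on one row (r = 1.3, σ = 0.35): ln 1.3 = 0.262; (0.819 − 0.262)/0.35 = 1.59, upper tail 5.6%; 0.819/0.35 = 2.34, upper tail 1.0%. The weighted mean is (5.6 + 2 × 1.0)/3 ≈ 2.5%, as it must be.

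**3. Three groups, and the effect of unbalanced ages.** Take three normal groups with SD 1 and means +s, 0 and −s (assumed). Shares above the common 97.5th percentile, in the order high, middle and low group:
- Equal groups, s = 0: 2.5% in each, so no harm.
- Equal groups, s = 0.5: 5.3%, 1.7% and 0.45%.
- Equal groups, s = 1: 6.8%, 0.64% and 0.02%.
- High group only 10% of controls (10/30/60), s = 0.5: 9.1% of the high group.
- Same 10/30/60 mix, s = 1: 16.7% of the high group.

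The error therefore depends on the age mix as well as on the age shift, and the age mix is not a balancing factor.

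**4. Price of limits by age group.** Equal groups would give 750/3 = 250 controls each, and 250/2 = 125 per sex within age. The true coverage of a sample 97.5th percentile taken as the *k*-th of *n* ordered values follows Beta(k, n + 1 − k):
- n = 750, k = 732: 95% range 96.2–98.5%; 18.75 observations expected above.
- n = 250, k = 245: 95.4–99.1%; 6.25 expected above.
- n = 125, k = 123: 94.3–99.5%; 3.1 expected above.

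**The case against.** **Age groups are clearly intended.** The objective, the primary outcome and Section 4 all say so, and Section 3.2.1 treats newborns separately when it discusses prematurity. By-age tables may simply have been left out of a condensed article. This part stands: no sentence says that limits will be pooled over age. A reader might infer that the sponsor plans one limit per sex for all ages, or that children will be misclassified, but the documents support neither as a certainty. They support the narrower statement that the described steps contain no age term.

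**Detail may sit in a fuller document.** Age boundaries, group sizes and table shells can fairly be left there, and their absence alone would be no finding. The contradiction between the stated outcome and the named factors remains.

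**The factor list may be illustrative.** The group-test wording speaks of various factors, and the ANOVA and Kruskal-Wallis tests would suit an age factor with three levels, although the four provinces would explain them too. This does not help the regression, whose terms are listed in full.

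**There are safeguards.** Cut-offs start from the kit manual (2.3.1) and are open to adjustment (2.3.4). Abnormal results are retested and then confirmed, and detected cases are displayed beside a control matched on age (3.3). Over-flagging would therefore mainly cost extra testing. A raised value hidden below the limit gets no such second look.

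**The size is assumed.** This is correct. The illustration also applies only to the 97.5th-percentile rule of Sections 2.3.4 and 3.2.1. It does not carry over to the mean ± 4 SD rule of 2.3.4 or the 0.5–99.5th percentiles of 3.2. The conflict between those rules is a separate matter.

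**Conclusion.** Wrong as written: the stated analysis does not deliver the stated primary outcome. This conclusion rests on the text alone and needs no assumption.

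The consequence is conditional. Read literally, the plan gives limits by sex over the whole range from 1 day to 18 years. If analyte levels differ by age, as Section 1 says, those limits flag too many healthy children where levels are naturally high, and sit too far above the normal range elsewhere. On the assumed inputs, 5.6–7.5% of healthy newborns and 0–1.0% of older children would lie above the limit instead of 2.5%, with the limit 14–76% above the older children's own. For an analyte with no age difference the error is nil. The documents give no figures from which to place any of the 51 metabolites on that range.

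**What to change.** - Define the three age groups in Section 2.2.2.
- Add age group to the balancing factors for whatever control recruitment remains. Equal groups are not essential, but each must be large enough for the percentile chosen.
- In 2.3.4 and 3.2.1, present reference intervals and cut-offs by age group first, and by sex within age only where sex matters and numbers allow.
- Add age to the factor tests, the regression in 3.2 and the high-risk versus healthy comparison, so that weight is read only alongside age.

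**Cost.** Mostly wording, since age is already collected (Table 1). Control recruitment began in October 2022, so balancing can act only on the children still to be enrolled. The statistical price is precision: with equal groups of 250, the true coverage of a sample 97.5th percentile ranges over about 95–99%, against 96–98.5% from 750. Splitting further by sex, to 125 per cell, leaves about three observations above the limit, so that split should be made sparingly.

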#### 3.2.1 Descriptive statistics and group comparison

Descriptive statistics and reference intervals for whole blood concentrations of 15 AAs, 35 ACs, and SuAc in healthy children divided into subgroups according to gender will be presented in tables. For each analyte in the healthy control group, the upper cut-off will be set above the 97.5^th^ percentile, while the lower cut-off will be set below the 2.5th percentile. Differences in the distribution of amino acids, acylcarnitines, and succinylacetone between groups, as determined using the Mann-Whitney and Kruskal-Wallis tests, will be noted in the table if found.

Cut-off values for analytes and their ratios for selective screening of AAD, OA, and FAOD presented in Table 3 will be pointed out. The results of determining the analytes in DBS in children of the healthy control group will be compared with those of previously published studies in other populations. According to the inclusion criteria, healthy newborns in the reference group must be full-term (born at 37–42 weeks). However, it should be taken into account that some of the newborns at risk for IEM are born prematurely. In this regard, it is also necessary to determine reference intervals for the concentrations of 15 AAs, 35 ACs and SuAc in dried blood spots of premature infants who do not have clinical symptoms of IEM.

Comparison of mean concentrations (Me, range) of analytes between groups of high-risk children and healthy controls will be presented.

#### 3.2.2 Statistical analysis by gender

The statistical analysis by gender (Mann-Whitney U-test) will be presented in groups of high-risk and healthy children. Comparison results by analytes taking into account gender, and body weight in the selective screening group and the group of healthy children will be presented in tables. In the presence of significant differences, in the form of box plots, where rectangles correspond to the 25th and 75th percentiles, the central and horizontal line is the median for each analyte. For all analytes, body weight scatterplots will be presented with a mean (M), median (Me), percentiles, and regression lines. Each analyte has its scale, measured in µmol/L.

### 3.3 Presenting detected cases

The results of LC-MS/MS in affected individuals will be presented as metabolic profiles. The metabolic profile of each affected individual will be placed next to the metabolic profile of a healthy individual from the control group, corresponding to gender, age, and place of residence. IEMs detected, their frequency, primary clinical manifestations, and main diagnostic markers in high-risk children confirmed by LC-MS/MS will be described in the tables. The average age of patients at the time of diagnosis will also be recorded. Table 4 displays the most common clinical manifestations in patients diagnosed with IEM. This list can be expanded by the results obtained in the study.

**TABLE 4 T4:** Common features encountered in children with different IEM (N = ***).

Variables	Number of patients (percent)
Developmental delay	
Neurological abnormalities	
Disturbed consciousness level	
Vomiting/dehydration	
Hyperammonemia	
Metabolic acidosis	
MRI brain abnormalities	
Infections	
Hypoglycemia	
Mental retardation	
Organomegaly	
Micro/macrocephaly	
Ophthalmic abnormalities	
Cardiomyopathy	
Seizures	
Tachypnea	
Thrombocytopenia	
Abnormal smell	
Hair growth disorders	
Osteoarticular anomalies	
Abnormal muscle tone	
Mutism	
Dysmorphia	

The baseline and repeated LC-MS/MS analysis results and biochemical confirmation in children diagnosed with IEM, according to the diagnosed disease, will also be presented. Demographic and laboratory data of confirmed cases detected by LC-MS/MS among 1,500 Kazakhstani children with suspected IEM will be presented in Table 5. Also, the table will include data on the reference values of the considered metabolites obtained in a sample of healthy controls.

**TABLE 5 T5:** Cases detected by LC-MS/MS among 1,500 children suspected IEM.

Metabolic disorder	Metabolite detected by LC- MS/MS (Abnormal parameter)	Positive cases, n (%)	Concentration mean (range) (μmol/L)	Cut-off limit (μmol/L)	References range (μmol/L)	Province (oblast), positive cases (n)
						
						

IEM, identified by selective screening with calculated frequencies for each disease, will be described separately for diseases belonging to the AAD, OA, and FAOD groups.

